**STATISTICAL TREATMENT OF RESULTS**

All outcomes will be analysed on an intention to treat basis including all randomised patients. Analyses will also be performed on a ‘per protocol’ basis (including only those who complete treatment) as a sensitivity analyses. Efficacy: We will employ multi-level modelling analyses for missing data using maximum likelihood methods (Everitt, 1998) to compare bulimic symptoms within and between groups. We will control for potential confounding variables (e.g. symptom levels at baseline), by using them as covariates in the analysis. Drop out rates will be compared across the two treatment groups using Pearson’s chi-square test. Predictors and Processes: Regression methods will be used to explore the relationship between potential predictor variables as described above in the hypotheses section and outcomes separately in the two groups. Treatment acceptability: patient satisfaction will be compared across the two treatment groups using t-tests or Mann-Whitney U tests, depending on the distribution.

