**Subsidiary hypotheses:**

1. Drop out will be lower in the ESM than the CBT group.
2. Acceptability of treatment will be superior in the ESM group, compared with the CBT programme.
3. ESM will be superior to the CBT programme in terms of the following variables, which will mediate or moderate symptom change:
   1. Reducing intolerance of emotional distress (moderator)
   2. Decreasing negative self-evaluation (mediator)
   3. Increasing adaptive emotional expression and processing (mediator)
   4. Increasing ability to regulate negative mood (mediator)
   5. Reducing self-criticism (mediator)
   6. Reducing negative beliefs about emotions (mediator)
   7. Reducing rumination (mediator)
   8. Reducing socially submissive behaviour (mediator)
   9. Improving social cognition (mediator)

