**Inclusion/exclusion criteria:**

Inclusion: patients referred to the SLAM Eating Disorder Service who fully (BN) or partially (EDNOS) fulfil DSM-IV criteria for bulimia nervosa.

Exclusion: insufficient knowledge of English or literacy levels to allow understanding of the intervention materials, active suicidality, severe substance dependence, diabetes or pregnancy. Informed written consent will be sought from patients at initial assessment.

**Proposed sample size:** Because ESM is a novel intervention, power was calculated on the basis of Chen *et al* (2003). A sample size of 30 in each arm of the study will have 80% power to detect a difference in means of -0.850 on the EDEQ Global score assuming that the common standard deviation is 1.15 using a two group t-test with a 0.05 two-sided significance level. Assuming a drop-out rate of 20% a sample size of 76 patients will be needed.

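### The sensitivity analysis the protocol names is limited to treatment completers, although the protocol predicts that completion differs by arm, so it cannot show whether the main model's missing-data assumption is tenable

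*Protocol*

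**What the plan says.** The Protocol's section on statistical treatment of results fixes the main analysis set: "All outcomes will be analysed on an intention to treat basis including all randomised patients". For efficacy it adds: "We will employ multi-level modelling analyses for missing data using maximum likelihood methods". Baseline symptom levels are given as an example of a covariate. The one analysis the section labels a sensitivity analysis is the per-protocol one ("including only those who complete treatment) as a sensitivity analyses").

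The first subsidiary hypothesis reads: "Drop out will be lower in the ESM than the CBT group". The statistics section plans a test of it: "Drop out rates will be compared across the two treatment groups using Pearson’s chi-square test". The sample size paragraph allows for drop-out with one overall rate: "Assuming a drop-out rate of 20% a sample size of 76 patients will be needed".

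The protocol does not name the assumption under which the maximum likelihood analysis is valid, and no analysis in it varies that assumption.

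**The concern.** Completing treatment happens after randomisation, and this trial expects it to depend on the arm. Selecting on it gives two groups of completers who may differ in prognosis for reasons unrelated to the effect of treatment on outcome. That matters because the protocol gives this comparison the role of testing how robust the main result is.

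The main model's weak point is a different one. Likelihood inference from incomplete data holds if outcomes are missing at random given what was observed. It fails if patients go unassessed because they are doing badly in ways the observed data do not capture. Dropping non-completers does not vary that assumption. A discrepancy may therefore be read as fragility when the main model is sound, and agreement may be read as reassurance when both estimates share the same bias.

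**Working it through.** **The plan's own figures.** Inputs from the sample size paragraph: "A sample size of 30 in each arm of the study will have 80% power", for a "difference in means of -0.850 on the EDEQ Global score", SD 1.15, two-sided 5%. The noncentral t distribution gives 80.4% power at 30 per arm, so the stated 80% reproduces. For drop-out, 30 / (1 − 0.20) = 37.5, rounded up to 38 per arm, or 76 in total. This reproduces too, and nothing below changes it.

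**Assumed inputs (not in the protocol).** Drop-out splits averaging the planned 20%: 20%/20%, 15%/25% and 10%/30% (ESM/CBT). Correlation r between staying and good outcome: 0.3 to 0.5. A negative ESM minus CBT difference favours ESM, as in the planned −0.85.

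**Step 1: bias of the unadjusted completers' contrast.** In a normal selection model with a proportion p staying, the completers' mean is better than that of all randomised patients by

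r × φ(z_p)/p × SD,

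where φ is the standard normal density and z_p the p-quantile.

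- p = 0.90: φ(z)/p = 0.195
- p = 0.70: φ(z)/p = 0.497
- Difference: 0.497 − 0.195 = 0.302
- r = 0.3: 0.302 × 0.3 × 1.15 = 0.104
- r = 0.5: 0.302 × 0.5 × 1.15 = 0.173

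| Drop-out ESM/CBT | r = 0.3 | r = 0.5 |
|---|---|---|
| 20%/20% | 0.00 | 0.00 |
| 15%/25% | +0.05 | +0.09 |
| 10%/30% | +0.10 | +0.17 |

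Positive values work against ESM. At 10%/30% the bias is 0.104/0.85 = 12% to 0.173/0.85 = 20% of the target difference, so a true −0.85 would appear as about −0.75 to −0.68.

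**Step 2: does the completers' result say anything about missing at random?** A large simulation took no true effect, a baseline-outcome correlation of 0.5, a stronger link of 0.7 between drop-out and its driver, and outcomes unobserved in all drop-outs. Completers' difference in points:

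| Drop-out | Driver | Unadjusted | Baseline-adjusted |
|---|---|---|---|
| 15%/25% | Baseline only (missing at random) | +0.06 | 0.00 |
| 15%/25% | Unobserved outcome (not at random) | +0.12 | +0.10 |
| 10%/30% | Baseline only (missing at random) | +0.13 | 0.00 |
| 10%/30% | Unobserved outcome (not at random) | +0.25 | +0.19 |

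In this setting, with baseline and one follow-up, the adjusted column approximates what a likelihood analysis of all randomised patients would give. In the baseline-driven rows the unadjusted completers' contrast departs from zero although the main model is right. In the outcome-driven rows the adjusted completers' contrast and the main model agree, and both are wrong. Neither agreement nor disagreement identifies which case applies.

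**Step 3: would the planned drop-out test give warning?** With 38 per arm, the power to detect a difference in drop-out is about 19% for 15% v 25% and 59% for 10% v 30%. A non-significant chi-square test would not make the completers' comparison safe.

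**The case against.** The case on the other side has real force.

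- *A statistical analysis plan may add other sensitivity analyses.* This stands. A reader might infer that the completers analysis is the trial's only robustness check, but the protocol shows only that it is the one named there. The point rests on the role the protocol assigns, not on missing detail.
- *The protocol never says the per-protocol analysis tests missing at random; it contrasts analysis sets.* True as to wording. Even as a contrast of sets, though, it selects on an event that the protocol predicts will differ by arm, so the sensitivity label promises more than it can deliver.
- *Stopping treatment is not the same as having a missing outcome.* This stands. Assessments are scheduled at 4 and 6 months for both groups, and nothing says that patients who stop treatment go unassessed. A reader might infer lost follow-up, but the document does not support it.
- *The size is assumed, and baseline covariates are planned.* This stands. The splits and correlations are not in the protocol, hypothesis 1 is a claim to be tested, and adjustment removes the part of the bias that baseline explains.
- *The bias is modest and works against ESM.* Completers would number about 38 × 0.9 = 34 and 38 × 0.7 = 27, so the standard error is 1.15 × √(1/34 + 1/27) ≈ 0.30 and the bias is about 0.35 to 0.6 of it. In the stated direction it cannot create a false claim for ESM. But that direction is an assumption too, and it reverses if patients leave because they feel well.

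**Conclusion.** The point holds in a limited form. The sensitivity analysis named in the protocol conditions on treatment completion, which the protocol expects to differ by arm, and it gives no evidence on whether missing at random is tenable for the maximum likelihood model. The figures of 0.10 to 0.17 points at 10% v 30%, and 0.05 to 0.09 at 15% v 25%, are unadjusted illustrations under the assumed r of 0.3 to 0.5. There is no bias if rates and selection are the same in both arms.

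Two stronger readings are not supported. The main intention-to-treat analysis is a reasonable choice and is not shown to be biased. Nor is bias against ESM certain: it needs completion to be related to outcome, a difference between arms, and worse patients being the ones who leave. The robustness check should be changed; the primary analysis stands.

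**What to change.** Label the completers analysis supplementary: a description of patients who finished treatment.

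Name as the sensitivity analysis a delta-adjusted (pattern-mixture) analysis in all randomised patients. The likelihood model itself imputes nothing, so unobserved outcomes would first be multiply imputed under the main model. They would then be shifted towards worse scores over a range such as 0 to 0.85 points, separately by arm. Report the shifts at which the conclusion changes. Leave observed outcomes as they are, including those of patients who stopped treatment. The upper end of the range is the planned difference; it is a convenient anchor, not a figure the protocol justifies.

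For scale, the difference moves by the shift times the proportion unobserved. A shift of 0.85 in ESM alone with 10% to 20% unobserved moves it by 0.085 to 0.17 against ESM. The same shift in both arms, with 10% and 30% unobserved, moves it by 0.85 × (0.10 − 0.30) = −0.17, in favour of ESM. This is why the arms need separate shifts.

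The cost is a change of wording and some extra analysis on the same data. The sample size stays at 76. The downside is that the completers result loses its role as the robustness check.

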**Randomisation, Blinding and Protection against Bias:**

At the point of referral patients’ suitability for participation will be checked by a clinician. If the patient is suitable and consents, she/he will be introduced to the research assessor who will complete the research assessment. The patient will then be randomised by a computerised system. Stratified randomisation will be used, stratifying for diagnosis (BN or EDNOS) to assign patients to one of the two trial arms. Patients will be told about the outcome of randomisation by the clinician. Throughout the trial every effort will be made to ensure that the assessor remains blind to the treatment condition. All therapeutic sessions will be taped and a random selection of these listened to by the research team to check for adherence to therapeutic model and quality of intervention.

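### Diagnosis stratifies the randomisation but is not named in the efficacy model, whose covariates are to be picked as possible confounders

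*Protocol*

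**What the plan says.** The Protocol section on randomisation, blinding and protection against bias sets one stratification factor: "Stratified randomisation will be used, stratifying for diagnosis (BN or EDNOS) to assign patients to one of the two trial arms". Both strata will be present, because the inclusion criteria admit patients "who fully (BN) or partially (EDNOS) fulfil DSM-IV criteria for bulimia nervosa".

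Under the statistical treatment of results, the efficacy analysis is described thus: "We will employ multi-level modelling analyses for missing data using maximum likelihood methods". The covariates follow in one sentence: "We will control for potential confounding variables (e.g. symptom levels at baseline), by using them as covariates in the analysis". Diagnosis does not appear in that section, either as a covariate or as a stratum. Drop-out is to be compared with an unstratified Pearson chi-square test. The sample size calculation assumes a two-group t-test without covariates.

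**The concern.** A factor is used for stratification because it is expected to matter for outcome. Balancing the arms on it removes its contribution to the sampling variation of the treatment difference. A model that leaves the factor out still counts that contribution in its residual variance, so the reported standard error is larger than the true one. The usual remedy is to analyse by the groups used to randomise, and here nothing in the statistical section does so.

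The rule given in its place is also badly framed. Under randomisation, baseline differences between arms arise by chance. Covariates earn their place by predicting outcome or by having been used in the allocation, not by being suspected confounders. A rule worded in terms of confounding points the analyst towards observed imbalance and away from the stratifier. At stake are some precision and power in a trial planned at almost exactly 80% power, and clarity about what the primary estimate is adjusted for.

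**Working it through.** **The plan's own figure.** The inputs from the sample size paragraph are "a difference in means of -0.850 on the EDEQ Global score", "the common standard deviation is 1.15", two-sided alpha 0.05 and 80% power.

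- Normal approximation: n per arm = 2 × (1.96 + 0.842)² × (1.15/0.85)² ≈ 28.7, rounded up to 29.
- Exact (noncentral) t: power is 0.790 at 29 per arm and 0.804 at 30, so 30 per arm is the smallest size that reaches 80%.
- Drop-out of 20%: 30/0.8 = 37.5, rounded up to 38 per arm, which is 76 in total.

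The stated 30 per arm and 76 in total both reproduce.

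**Effect of leaving diagnosis out.** Let R² be the share of outcome variance explained by diagnosis after allowing for baseline symptoms. The protocol gives no value, so 2%, 5% and 10% are assumed. Allocation is taken as exactly balanced within strata at 30 per arm, and a two-sample comparison stands in for the treatment contrast of the multi-level model.

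- True SE = σ × √(1 − R²) × √(2/n); SE reported without diagnosis ≈ σ × √(2/n). Their ratio is 1/√(1 − R²).
- True type I error without diagnosis = 2 × [1 − Φ(1.96/√(1 − R²))].
- Power without and with diagnosis comes from 40,000 simulated trials per scenario, with difference 0.85 and SD 1.15. The simulation put 21 of 30 patients per arm in one stratum, also an assumption.

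| Assumed R² | Reported SE too large by | True type I error | Power without diagnosis | Power with diagnosis | Difference (points) |
|---|---|---|---|---|---|
| 0 | 0% | 0.050 | 0.805 | 0.805 | 0 |
| 0.02 | 1.0% | 0.048 | 0.805 | 0.811 | about 0.5 |
| 0.05 | 2.6% | 0.044 | 0.809 | 0.823 | 1.4 |
| 0.10 | 5.4% | 0.039 | 0.811 | 0.839 | 2.8 |

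Worked line for R² = 0.10: 1/√0.90 = 1.054; 1.96 × 1.054 = 2.066; 2 × [1 − Φ(2.066)] = 0.039.

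**How to read the table.** The SE ratio and type I error depend only on R². They therefore carry over to a model already adjusted for baseline symptoms, provided R² is the residual share. The power columns also depend on the SD. They treat 1.15 as the SD after baseline adjustment, so they indicate the size of the effect and do not predict this trial's power.

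**The case against.** The strongest objection is that the covariate sentence introduces baseline symptoms as an example only. Diagnosis is neither listed nor ruled out, and a full covariate list is commonly left to a statistical analysis plan, which is not at hand. This stands in part. A reader might infer that the model omits diagnosis and that its standard errors therefore ignore the stratification. The protocol does not say so, and an open list cannot establish an omission. The point is that the sentence fixes a rule, that the rule is poorly framed for a randomised comparison, and that it does not bring in the one factor the design stratifies on.

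A reader might also infer that covariates will be chosen after imbalances or results are seen, so that the treatment estimate could be selected. The wording does not prevent this, but nothing in it makes adjustment depend on observed imbalance or proposes data-driven selection. An unfinished list alone would be detail for an analysis plan.

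Three objections to the size also stand.

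- The R² values are assumed.
- The strata separate full from partial fulfilment of the bulimia criteria, which plausibly overlaps with baseline symptom level. The residual share could be small or nil.
- The loss of type I error requires restricted allocation within strata, such as blocks, and the protocol describes none. With simple randomisation within strata, a test without diagnosis keeps its nominal level.

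Finally, Pearson's test for drop-out is valid and at worst mildly conservative, and drop-out is a subsidiary hypothesis. Stratifying that test is a preference.

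**Conclusion.** The point holds as a modest specification weakness. The design stratifies on diagnosis, the analysis text does not name it, and the covariate rule rests on the wrong principle for a randomised trial.

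Harm from omission needs three conditions: diagnosis is in fact left out, allocation is balanced within strata, and diagnosis predicts outcome beyond baseline symptoms. Under an assumed residual R² of 2% to 10%, the cost is a standard error about 1% to 5% too large, a true type I error of about 0.048 to 0.039, and about 0.5 to 3 points of power. The error is on the conservative side: leaving diagnosis out does not inflate the type I error. With a residual R² of zero there is no effect. The planned 30 per arm and 76 in total are unaffected.

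**What to change.** In the efficacy part of the statistical section, replace the sentence on confounders with one on these lines: the primary model adjusts for the baseline value of the outcome and for diagnosis stratum (BN or EDNOS); any further covariate is specified before outcome data are seen. Other prognostic covariates remain legitimate if they are fixed in advance.

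Comparing drop-out with a test stratified by diagnosis (Mantel-Haenszel) would be consistent with this, but is optional.

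Diagnosis is already recorded for randomisation, so no new data are needed. The change costs one sentence and one degree of freedom, and the sample size stays as it is.

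### The process analysis is fixed as regressions run separately in each arm, which cannot estimate the mediation that hypothesis 3 claims and states no contrast for moderation; item 3.1 also labels a post-randomisation change a moderator

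*Protocol*

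**What the plan says.** Under Subsidiary hypotheses, the third hypothesis reads: "ESM will be superior to the CBT programme in terms of the following variables, which will mediate or moderate symptom change". Nine changes follow. Eight are labelled mediators, for example "Decreasing negative self-evaluation (mediator"). The first is labelled differently: "Reducing intolerance of emotional distress (moderator").

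Under Statistical Treatment of Results, the part on predictors and processes opens with "Regression methods will be used to explore the relationship between" and continues with "potential predictor variables as described above in the hypotheses section and outcomes separately in the two groups". It gives no pooled model, treatment term, treatment-by-variable interaction, indirect effect or later comparison of the two arms' slopes.

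Two other sentences in that section bear on the point. The multi-level model is named "to compare bulimic symptoms within and between groups", so it covers symptoms and not the process variables. The section also opens with a general rule: "All outcomes will be analysed on an intention to treat basis including all randomised patients".

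**The concern.** Hypothesis 3 is a claim about the difference between treatments: ESM changes certain variables more than CBT does, and those variables explain or alter the difference in symptoms. Mediation needs the effect of arm on the mediator and the effect of the mediator on outcome with arm held fixed. Moderation needs the treatment effect to vary with a characteristic present before treatment, which is an arm-by-variable interaction or an equivalent contrast. A regression inside one arm contains no treatment contrast at all.

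The label in item 3.1 adds to the mismatch. A reduction that ESM is predicted to produce is a consequence of treatment, of the same kind as the eight changes labelled mediators. It cannot serve as a moderator of the treatment effect.

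At stake is the process claim behind ESM. If the plan is followed as written, within-arm correlations between process change and symptom change could be reported as evidence of how ESM differs from CBT, which they do not show.

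**Working it through.** **The plan's own figure.** From Proposed sample size: difference 0.850, SD 1.15, two-sided 0.05, 80% power. The standardised difference is 0.850/1.15 = 0.739. The two-sample t-test needs 29.7, so 30 per arm, with power 0.804 at 30. With 20% drop-out, 30/0.8 = 37.5, so 38 per arm and 76 in total. Both figures reproduce. They give the arm sizes used below: 30 (completing) and 38 (randomised).

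**Mediation.** Let a be the effect of arm on the mediator and b the mediator-outcome slope with arm held fixed. The indirect effect is a × b. A within-arm regression estimates b only, because a is a difference between arms. Simulation with 30 per arm, standardised variables, b = 0.4 and no direct effect (all assumed), 2,000 trials per row:

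| a (SD) | True a × b | Mean slope, arm 1 / arm 2 | Mean pooled estimate of a × b |
|---|---|---|---|
| 0 | 0 | 0.406 / 0.402 | -0.004 |
| 0.5 | 0.20 | 0.402 / 0.404 | 0.201 |
| 1.0 | 0.40 | 0.400 / 0.408 | 0.403 |

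The arm-separate output is the same in all three rows. Only the pooled model tells them apart.

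**Moderation, as illustration only.** Suppose a variable has the same true correlation r with outcome in both arms, so there is no moderation, and suppose a reader declares moderation when exactly one arm is significant. The protocol states no such rule and gives no r. By Fisher's z, within-arm power is p = P(|Z + atanh(r) × √(n − 3)| > 1.96), and the chance that exactly one arm is significant is 2p(1 − p). Example: r = 0.35, n = 38 gives 0.3654 × √35 = 2.162, p = 0.58, and 2 × 0.58 × 0.42 = 0.49.

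| r | p, n = 30 | Exactly one arm, n = 30 | p, n = 38 | Exactly one arm, n = 38 |
|---|---|---|---|---|
| 0.1 | 0.08 | 15% | 0.09 | 17% |
| 0.2 | 0.18 | 30% | 0.22 | 35% |
| 0.3 | 0.36 | 46% | 0.45 | 49% |
| 0.35 | 0.48 | 50% | 0.58 | 49% |
| 0.4 | 0.60 | 48% | 0.71 | 41% |
| 0.5 | 0.81 | 30% | 0.90 | 18% |
| 0.6 | 0.95 | 10% | 0.98 | 3% |

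The function 2p(1 − p) cannot exceed 0.50, and correlations of 0.3 to 0.4 lie near that peak. A simulation of 4,000 trials per value at 30 per arm agrees: 47%, 50%, 48% and 29% at r = 0.30, 0.36, 0.40 and 0.50. The interaction test in the same trials rejected in 5.2%, 4.9%, 5.4% and 5.7%.

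**Item 3.1 beside the other items.** All nine are worded as changes that ESM should produce more than CBT. Nothing sets the first apart except its label.

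**The case against.** The other side has several good points.

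- **Hypothesis 3 is not unanswerable as a whole.** A reader might infer that it is. Its superiority part is an ordinary between-arm comparison of secondary outcomes, covered by the general intention-to-treat sentence, and the detailed model can properly sit in an SAP. This stands: only the mediation and moderation clause is affected.
- **The process aim is not left empty.** The Aims section speaks of exploring processes and predictors in these treatments, and within-arm regressions do describe predictors of outcome in each. The wording is exploratory and the hypothesis is subsidiary. This stands, but an exploratory estimate must still target the quantity in the hypothesis.
- **Separate regressions do not rule out a test of moderation.** Slopes and standard errors for a baseline variable could be contrasted between arms afterwards, which amounts to an interaction test. This stands. The accurate criticism is that no such contrast is stated. For mediation, contrasting slopes does not supply the missing effect of arm on the mediator.
- **The one-arm-only rule is not in the protocol, and a false discordance of 41% to 50% would hold only for r of 0.3 to 0.4.** This stands, so the figure is given over a wider range and as illustration.
- **The moderator label is one word, and distress tolerance is measured at baseline.** True. A baseline moderator analysis is feasible, which makes the correction easy; the label as written is still wrong.

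**Conclusion.** The point holds in a limited form. The protocol does not merely leave this analysis to an SAP: it fixes it as separate regressions by arm, and that choice does not fit the mediation and moderation clause of hypothesis 3. An SAP that followed the sentence would inherit the mismatch.

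For mediation the consequence does not depend on the assumed values: within an arm the effect of treatment on the mediator is not estimable. For moderation the gap is an unstated contrast. Its possible size, about 3% to 50% false discordance against about 5%, rests on an assumed r of 0.1 to 0.6, on equal correlations in both arms, and on a reading rule that the protocol does not contain. It should not be quoted as the trial's error rate.

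The change should be made, but it concerns a subsidiary, exploratory analysis and does not touch the primary comparison.

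**What to change.** In Statistical Treatment of Results, replace the arm-separate regressions with models that pool both arms.

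- **Moderation:** outcome on arm, baseline symptom score, baseline distress tolerance, and arm × baseline distress tolerance.
- **Mediation, for mediators with a listed measure:** (a) the 4-month mediator on arm, adjusted for its baseline; (b) the 6-month outcome on the 4-month mediator, adjusted for arm, baseline mediator and baseline symptoms; (c) the indirect effect with a bootstrap interval.
- **4-month symptoms:** do not adjust for these in the main mediation model. They are measured at the same end-of-treatment visit as the mediator and may lie on the causal path, so adjustment could remove much of the effect of interest. Use it at most as a sensitivity analysis, read as mediation of change from 4 to 6 months.
- **Item 3.1:** reword it so that baseline intolerance is the moderator and its reduction a mediator.
- **Status:** keep all of this exploratory.

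The cost is wording in two sections and modest analysis work within the planned assessments at baseline, 4 and 6 months. There are two limits. The Secondary outcomes list names no clear scale for emotional expression and processing (item 3.3) or for regulating negative mood (item 3.4), so those models need a measure identified first. Intervals for interactions and indirect effects will also be wide, because the sample size was set for the primary mean difference.
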